## Abstract

**Background:**

The goal of this project is to evaluate the implementation of an integrated and interdisciplinary program for prevention and management of cardiometabolic risk (PCMR). The intervention is based on the Chronic Care Model. The study will evaluate the implementation of the PCMR in 6 of the 12 health and social services centres (CSSS) in Montréal, and the effects of the PCMR on patients and the practice of their primary care physicians up to 40 months following implementation, as well as the sustainability of the program. Objectives are: 1-to evaluate the effects of the PCMR and their persistence on patients registered in the program and the practice of their primary care physicians, by implementation site and degree of exposure to the program; 2-to assess the degree of implementation of PCMR in each CSSS territory and identify related contextual factors; 3-to establish the relationships between the effects observed, the degree of PCMR implementation and the related contextual factors; 4-to assess the impact of the PCMR on strengthening local services networks.

**Methods/Design:**

The evaluation will use a mixed design that includes two complementary research strategies. The first strategy is similar to a quasi-experimental "before-after" design, based on a quantitative approach; it will look at the program's effects and their variations among the six territories. The effects analysis will use data from a clinical database and from questionnaires completed by participating patients and physicians. Over 3000 patients will be recruited. The second strategy corresponds to a multiple case study approach, where each of the six CSSS constitutes a case. With this strategy, qualitative methods will set out the context of implementation using data from semi-structured interviews with program managers. The quantitative data will be analyzed using linear or multilevel models complemented with an interpretive approach to qualitative data analysis.

**Discussion:**

Our study will identify contextual factors associated with the effectiveness, successful implementation and sustainability of such a program. The contextual information will enable us to extrapolate our results to other contexts with similar conditions.

**Trial registration:**

ClinicalTrials.gov: NCT01326130

## Background

Evaluation of effective and sustainable interventions in chronic disease management and of their implementation in various contexts is essential to guide such initiatives in Canada. One initiative that seems promising but presents a challenge to be addressed by decision makers at all levels is the creation of primary care-centred integrated networks that foster and are congruent with the development of local services networks. Our study findings will support efforts to institute local integrated services networks throughout Canada.

The Agence de la santé et des services sociaux de Montréal (ASSSM) has commissioned our team to help evaluate the implementation of an integrated and interdisciplinary cardiometabolic risk (diabetes and hypertension) management and prevention program. The intervention is based on the Chronic Care Model (CCM), in a context where integrated services networks are created. Although shorter-term effects can be detected and the implementation process documented over a short time period, longer-term effects on patients registered in the program and on the practices of participating physicians, as well as the sustainability of implemented actions, require a long enough observation period to take place. The project is scheduled to last 40 months.

### Some epidemiological data

The growing burden of chronic diseases such as diabetes and their impact on the health system are now obvious [1]. Population ageing and changes in lifestyles, especially in terms of diet and sedentarity, are markedly responsible for this increased burden. In 2006-07, nearly 6 million Canadians aged 20 years and older were living with diagnosed hypertension (24.0% of women and 21.3% of men) [2]; over 2 million Canadians aged 20 years and older, or 8.0% of the population, were diagnosed with diabetes (7.5% of women and 8.6% of men) [3]. The age-adjusted prevalence of hypertension in Canada rose 52% from 1998-99 to 2006-07; for diabetes, it increased by 21% between 2002-03 and 2006-07. In 2006-07, 5.1% of Canadians aged 20 years and older were living with both diabetes and hypertension; 22.7% of adults with hypertension also had diabetes, and 62.8% of adults with diabetes also had hypertension [2]. These data demonstrate the relevance and significance of considering the two diseases together. In addition, both have common risk factors and complications.

### Recommendations - Hypertension and diabetes

The most recent clinical practice guidelines for diabetes [4,5] and hypertension [6] give evidence-based recommendations pertaining to follow-up of people with diabetes or hypertension. Optimization of glycemic control is fundamental to adequate patient management. Glycated hemoglobin (HbA1c) can reliably assess average glycemia over the past 3 to 4 months [7] and is a good indicator of treatment efficacy [5]. In most patients with diabetes, treatment must achieve a median HbA1c value ≤ 7.0% to reduce the risks of microvascular [8] and macrovascular [9] complications. Hypertension guidelines set the target level for blood pressure at 140/90 mm/Hg; the target level for people with diabetes is 130/80 mm/Hg.

For optimal glycemia and hypertension control, the guidelines target lifestyle modification (diet, physical activity and smoking cessation) and risk factor management (dyslipidemia and obesity), in addition to pharmaceutical treatment. Support for disease self-management is also an integral part of an effective strategy for chronic disease management. Individuals with chronic diseases must cope on a daily basis with the symptoms and consequences of the disease, and are mostly responsible for enacting appropriate strategies (e.g. lifestyle modifications, measurement of blood glucose levels or of blood pressure at home) that will enable them to maintain a satisfactory quality of life [10]. Self-management is considered to be an effective way to narrow the gap between the needs of people with chronic diseases and the capacity of the health system to respond to those needs.

Moreover, the guidelines indicate that although short clinical interventions increase the likelihood that patients adopt and maintain healthy lifestyle habits, interdisciplinary care approaches are more effective [12,13]. Care must be provided systematically and supported by organizational interventions (e.g. computerized databases, decision trees, patient and team member recall systems). It is essential that the family physician, who ensures continuity of care, and the patient care team coordinate care and share clinical information. In a care model based on collaboration, the care team should be given appropriate support and training (e.g. through the participation of a specialist). Studies of chronic care management programs indicate that the Chronic Care Model (CCM) developed by Wagner et al. [14] contains the necessary elements to improve processes of care as well as the health and quality of life of patients with chronic diseases [15,16].

### The Chronic Care Model

A number of care models have been developed to improve chronic disease management. The Chronic Care Model [14] is the one most often used. It is based on integrating services at different levels of the health system, and revolves around six interrelated elements of care organization: 1) delivery system design (coordinated and integrated multidisciplinary teams with systematic sharing of clinical information); 2) self-management support for patients; 3) decision support (interventions designed to improve providers' knowledge and skills); 4) development of a clinical information system (computerized patient registry and computerized evaluation and follow-up tools); 5) use of community resources; and 6) healthcare organization centred on chronic illness. The CCM posits that better outcomes are likely to result from interactions between a proactive team of well-prepared professionals and active, informed patients [17].

Several studies, particularly of diabetes patients, have shown that interventions based on CCM components improve processes and outcomes, and reduce costs and service utilization among patients with chronic illnesses [18]. However, most of these studies focus on management of single morbidities, from a disease rather than case management perspective [19]. Yet, people with chronic diseases often present multiple comorbidities. To provide effective care, the CCM should be oriented toward case management to take into account multiple morbidities [19,20].

Moreover, the literature indicates that primary care services are best suited to provide chronic disease management, although few studies have analyzed factors facilitating implementation of the CCM in primary care settings [19,20]. A number of factors that facilitate or hinder implementation of the CCM in various contexts have been reported in the literature [14,21-24]. A lack of human and financial resources and the absence of appropriate clinical information systems are the most common barriers reported. An organizational culture that fosters change, the quality of managerial leadership, management strategies that frame organizational changes (objectives clearly defined, organizational strategic plan developed, and trusting relationships among stakeholders), physician support, vision and values related to changing practices, medical leadership that supports innovation, and the presence of championing physicians are all significant to successful implementation.

### Implementation of local health networks

Chronic illness management requires better integration of services designed for individuals affected with such diseases. It is in part to meet these needs that, in 2004, 95 health and social services centres (CSSS) were created in Québec, 12 of which being in Montréal. The Centres resulted from the merging of local community health centres, long-term care facilities and, in most cases, a hospital. The goal of this new entity is to bring health services closer to the population, make them more accessible and improve their coordination and continuity in each territory. CSSS have also been given the mandate to set up local services networks by encouraging collaboration among organizations and partners in their territories, more particularly primary care services [25].

Several strategies can be adopted to create local services networks, one of which is to set up integrated services networks based on disease or population target groups. Studies have shown that implementation of health networks is facilitated by the development of initiatives that foster integration of services for targeted groups of patients with chronic illnesses or with distinct demographic characteristics [26-29]. In addition, clinical integration is a prerequisite to systemic integration [30]. In this sense, by favouring the establishment of integrated services networks, the CCM is a first-rate instrument to create local services networks and to consolidate their implementation.

### Initiatives in Montréal and implementation of a cardiometabolic risk program

The Agence de la santé et des services sociaux de Montréal (ASSSM) has undertaken activities designed to improve management of chronic illnesses and inspired by the Chronic Care Model. In 2006, following a strategic initiative launched by the ASSSM, the CSSS Sud-Ouest-Verdun set up a diabetes referral centre. Since then, the program has become a model for the other CSSS in Montréal, who have shown an interest in developing similar programs in their territories. Due to the frequent association between diabetes and hypertension, the ASSSM has recommended adding the latter to the program. The ASSSM proposes to continue to implement the integrated and interdisciplinary program for prevention and management of cardiometabolic risks (PCMR) first in six CSSS territories in Montréal (including the CSSS Sud-Ouest-Verdun), and then eventually in all CSSS in Montréal. Each CSSS will implement the program with the perspective of having an integrated care network in its territory, taking into account its specific organizational context. The program aims to improve diabetes and hypertension control among the target clientele (early detection, control of risk factors, optimal non-pharmacological and pharmacological management); enhance the quality of life of people with dysglycemia and/or hypertension; consolidate primary care case management and optimize use of specialized services; and strengthen links with various partners to offer integrated services in the CSSS territory. Targeted clienteles are adults with marginal fasting glycemia, or glucose intolerance, or diabetes treated with diet only, or diabetes treated with monotherapy, or diabetes treated with more than one medication if HbA1c ≤ 8.0%; as well as adults with hypertension with BP in the doctor's office ≥ 140/90 mm Hg (if diabetic, with BP ≥ 130/80).

The PCMR anticipates implementing a **clinical process **in each CSSS that aims, over a two-year period, to change lifestyle habits, control biological indicators, prevent complications and support patient self-management. Clinical interventions include group educational sessions given by the nutritionist, nurse, kinesiologist, pharmacist and psychosocial worker; individual follow-up by the nutritionist and the nurse; participation in a physical activity program; monitoring of biological parameters; and referral to specialists, as needed. In each CSSS, follow-up and educational activities are provided by a cardiometabolic risk education centre's interdisciplinary team, complementarily with medical follow-up provided by the primary care physician. Details of the program are available from the authors upon request.

In addition to implementing the clinical process, the PCMR provides **practice support to primary care physicians **for management of targeted patients by consolidating continuing medical education programs and developing clinical tools and documentation to ensure that practices are standardized in accordance with the guidelines. Lastly, the PCMR plans, in a perspective of integrated services networks, **to establish and consolidate links among various partners **(e.g. primary care clinics, cardiometabolic education centre, resources in specialized care, pharmacists) and especially to consolidate service pathways that facilitate primary care access to specialized health services. Moreover, mechanisms will be put in place to ensure the clinical information needed for effective patient management and monitoring circulates fluidly among professionals. The ASSSM plans to implement a computerized regional registry for chronic diseases that includes anthropometric and biochemical data on the clientele being followed. For professionals of the cardiometabolic education centres, the registry will serve as a clinical tool, while it will be used as a communication tool by attending physicians and for project evaluation.

Participating CSSS are responsible for implementation of the PCMR, and for setting up local coordination committees to oversee project planning and implementation, and to follow up on the project evaluation. In each CSSS, the local committee will set up a clinical committee responsible for the clinical tools and contents needed to implement the project. The ASSSM will provide regional leadership and organizational support required to implement the program in CSSS. Mechanisms will be put in place to encourage primary care physicians to participate (e.g. early involvement of primary care physicians in developing the program and within local coordination committees; support for the project from professional associations; meetings in primary care clinics to enlist the cooperation of physicians). Furthermore, financial compensation is available from the RAMQ (Québec's health insurance board) for general practitioners who help organize clinical projects in a CSSS territory.

### Conceptual framework for program evaluation

The starting point for our conceptual framework (Figure 1) is the implementation of the program, which takes place over a 40-month period and includes three phases: initiation, development and sustainability. The latter takes shape by integrating PCMR activities into regular CSSS planning. The effects observed on patients and on medical practice vary depending on the degree to which the PCMR is implemented. Program implementation is influenced by a set of contextual factors that have various influences [31-33]. The ASSSM, which shares responsibility with the CSSS for meeting population needs, sponsors the project and has a determining and highly influential effect through the resources it allocates to the project. The CSSS also has a direct influence on the program due to its organizational characteristics and its structure, as well as to the role played by its human, material, technological and other resources. Moreover, by creating a critical mass of resources accessible to organizations in the territory, the CSSS introduces into the local services network incentives that can lead to greater inter-organization collaboration, which then favours the development of integrated networks. In this sense, the influence of the ASSSM and the CSSS on the development of local services networks can be seen as coercive [33,34]. Other organizations in the local network can also influence network implementation. For instance, the presence of Family Medicine Groups (FMG) can provide benchmarks and models that other medical clinics can emulate (mimetic influence). Similarly, specialized hospitals and other resources can influence the nature and degree of collaboration and networking. Finally, professional associations and their leaders can facilitate or hamper network implementation. In that respect, the Association des médecins omnipraticiens de Montréal, the Département régional de médecine générale and its local representatives as well as other leaders in the field greatly influence collaboration among local service network organizations as well as implementation of networks (normative influence). These various influences are exerted within a dynamic environment and contribute to its evolution.

**Figure 1 F1:**
[figure not shown]
**Conceptual framework**.

### Research Questions and Objectives

#### Objective 1

To evaluate the effects of the PCMR and their persistence on patients registered in the program and the practices of their primary care physicians, by implementation site and degree of exposure to the program.

For patients, the program should result in improved lifestyle habits and better control of their diabetes and/or their hypertension. Chronic illness management and follow-up should be noticeably improved, as should patient self-management and quality of life. Closer and better coordinated follow-up should also improve certain elements of the patients' experience of care with their primary care physicians (continuity of information, comprehensiveness and perceived outcomes of care). Finally, controlling their condition is likely to lead patients to use health services more appropriately (fewer visits to emergency and fewer hospitalizations for problems related to diabetes or hypertension). In all likelihood, these effects on patients will vary depending on the setting (CSSS) and degree of exposure to the PCMR. As regards medical practice, PCMR implementation should be reflected in participation in the program (continuous medical education activities, use of clinical tools, referral of patients to cardiometabolic risk education centres), interprofessional collaboration and patient management interventions. Persistence of effects on both patients and medical practice remains to be demonstrated.

#### Objective 2

To assess the degree to which the PCMR has been implemented in each participating CSSS territory (local services network) and identify the context-related factors (coercive, normative and mimetic pressures) that could explain the level of implementation.

The aim is to answer the following research questions: To what degree has each setting implemented the program? What contextual factors facilitate or hinder program implementation? To what extent is program sustainability assured: does the PCMR fit into CSSS program activities?

#### Objective 3

To establish the relationships between the observed effects (Objective 1), degree of implementation of the program and contextual factors (Objective 2).

This objective implies the following research questions: How do variations in PCMR implementation influence the effects observed? To what extent do the contextual factors that facilitate or hinder program implementation influence the observed effects?

#### Objective 4

To assess the impact of implementing the PCMR on strengthening local services networks.

This objective concerns the following research question: To what degree does implementing this program help consolidate local networks by establishing closer and long-lasting links among service providers in the CSSS territory?

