Data will be collected in three phases, as per the program implementation stages. Semi-structured interviews with individuals from the ASSS and CSSS responsible for program implementation are scheduled for the beginning of the project (start-up phase). They will provide an initial portrait of regional services organization related to the activities of the program being implemented and will document the program components (objectives and purposes, roles and actors involved, resources and activities). They will also be used to define the dynamics in each implementation site. Interviews with respondents from each territory will focus on local historical contexts of interventions with people at risk of or who have diabetes or hypertension; organizational contexts of the CSSS; PCMR activities already in place and their components; local resources allocated; number of medical clinics and physicians involved; and number of patients targeted by the program. A second and third round of semi-structured interviews with local and regional respondents will be conducted 20 and 40 months after the beginning of the program. They will document PCMR activities actually implemented and degree of program implementation, activities set up to integrate the PCMR into the CSSS's regular activities, and obstacles and facilitators encountered. The questionnaires for physicians will also document barriers and facilitators. These contextual determinants will be grouped by dimension and conveyed with descriptive variables. The interview grids used at the beginning of the implementation of the project are included in Additional files 7a and 7b. Data collection tools that will be used 20 and 40 months after the beginning of the program will be constructed after analysis of the data collected at the beginning of the implementation of the project.

Based on the information collected throughout the project, a descriptive analysis of each case (implementation setting) will be performed. Six monographs, one for each setting, will describe the phases of PCMR implementation and its explanatory factors.

#### Objective 3

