This objective concerns the PCMR's influence on interorganizational collaboration and networking among local services networks. We are interested in mechanisms for collaboration that exist between CSSS and primary care organizations in the territories and health care and services providers, as well as their evolution over time. We will use the framework developed for our previous project [36]. Interorganizational collaboration within local services networks will be documented at the beginning of the project, based on the results of our previous project [36], which looked at this issue for CSSS territories in Montréal in 2010 (questionnaire in Additional file 8). A questionnaire administered to key CSSS informants 40 months after project onset will document the evolution of interorganizational collaboration within local services networks in relation to PCMR implementation (Additional file 9). By becoming a model of service integration, the PCMR is in fact likely to form a best practice that has a mimetic influence on local services network partners, and eventually lead to the creation of other networks (e.g. for COPD) and, more generally, to interorganizational collaboration. The questionnaire will be adapted from questionnaires used in our previous project [36] to explore territorial contexts. Questions on the PCMR's influence on interorganizational collaboration and networking within local services networks will also be included in the final questionnaire for physicians participating in the program.

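### Objective 4 asks about long-lasting links, but its network-wide measure has one wave after the start, at month 40 when the project ends, so durability is only weakly supported

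*Protocol article*

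**What the plan says.** In the section on research questions and objectives, Objective 4 asks: "To what degree does implementing this program help consolidate local networks by establishing closer and long-lasting links among service providers in the CSSS territory". The methods for Objective 4 restate the interest as collaboration mechanisms between CSSS, primary care organizations and "health care and services providers, as well as their evolution over time".

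The same methods text names three sources:

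- **Baseline.** "Interorganizational collaboration within local services networks will be documented at the beginning of the project", taken from the results of the team's earlier project for 2010.
- **Follow-up.** "A questionnaire administered to key CSSS informants 40 months after project onset will document the evolution of interorganizational collaboration within local services networks".
- **Physicians.** Questions on the program's influence on collaboration and networking "will also be included in the final questionnaire for physicians participating in the program".

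The Background section says: "The project is scheduled to last 40 months".

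Two other sources touch on links but sit under other objectives. Under Objective 2, "A second and third round of semi-structured interviews with local and regional respondents will be conducted 20 and 40 months after" the program begins; these rounds cover what was implemented and to what degree, steps to embed the program in routine CSSS work, and obstacles and facilitators. Under Objective 1, the physician questionnaires at 12, 24 and 36 months include questions about dealings with specialized services.

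**The concern.** The question claims two things, and the assigned measurements suit only one of them. Comparing the 2010 baseline with month 40 addresses whether collaboration has become closer. Whether it lasts depends on what happens between the start and month 40, or after month 40. On the stated schedule, the network-wide measure observes neither.

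A territory whose links were set up early and held, and one whose links came and went with a fresh set in place at month 40, could give similar endpoint results. If both were described as consolidated, the word long-lasting would rest on little evidence. This matters because the article presents the effect on local networks as one of its four objectives and as a strength of the study.

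**Working it through.** The article gives no sample size, power or error figure for Objective 4, so there is no planned figure to reproduce. The check sets the measurement schedule against the question. I assume that the project and program clocks start together and that patient recruitment starts at month 0.

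**Step 1: the sources assigned to Objective 4.**

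| Source | Before start | After start | What it covers |
|---|---|---|---|
| Key CSSS informants | 1 (2010 results) | 1 (month 40) | Collaboration across the local network |
| Final physician questionnaire | 0 | 1 per physician | Perceived influence of the program on collaboration |

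Observation left after the network-wide wave: 40 − 40 = 0 months.

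**Step 2: what two points can show.** The difference between baseline and month 40 is identifiable. The age of a link present at month 40 is not, unless the questionnaire asks about timing in retrospect. A link formed after baseline and lost before month 40 appears at neither point.

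**Step 3: does the physician source add a repeated measure?** Each physician answers the Objective 4 items once. Physician waves are timed from the first attendance of one of that physician's patients at the education centre. The latest first attendance that still allows each wave within 40 months is:

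- 12-month wave: 40 − 12 = month 28
- 24-month wave: 40 − 24 = month 16
- 36-month wave: 40 − 36 = month 4

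If the final questionnaire means the 36-month wave, only physicians whose first patient attended in about the first four months contribute. If it means each physician's last wave, more contribute, but still once each.

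**Step 4: sources not assigned to Objective 4.**

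- *Interviews at months 20 and 40.* Two rounds after the start, 40 − 20 = 20 months apart. Building links among partners is itself a component of the program, so a record of what was implemented can touch on links. Interorganizational links are not among the listed topics.
- *Physician items on specialized services.* Up to three waves after the start, within the limits in Step 3. They concern one kind of relationship and do not cover the wider network of CSSS, primary care organizations and other providers.

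**Step 5: how duration is handled elsewhere.** For patients under Objective 1, persistence has a dedicated 36-month postal questionnaire, a year after program follow-up ends (36 − 24 = 12 months). Under Objective 2, sustainability has the two later interview rounds. Objective 4 makes a comparable claim about duration without a stated repeated measure or criterion.

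**The case against.** The strongest reply is that the plan holds more evidence on lasting links than the Objective 4 text lists.

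- Establishing links is a program component, so the month-20 and month-40 interviews on implemented activities can record it twice.
- Those interviews also cover absorption of the program into routine CSSS work, which the conceptual framework treats as the sustainability phase.
- Physicians report repeatedly on specialized services, and the design section says that the quantitative and qualitative strands will be triangulated.
- The month-40 questionnaire (Additional file 9, not shown) is meant to document how collaboration evolved and may ask when links began.
- The limitations section concedes that 40 months may be too short to judge sustainability over the longer term.

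Much of this stands, and it rules out stronger readings. A reader might infer that links are measured only once after the start, that lasting links cannot be told from recent ones, or that half of Objective 4 is unanswerable. The documents support none of these: partial repeated evidence exists, and the unseen questionnaire may ask about timing. Nor do they support any estimate of link turnover, since they give no rates of formation or loss.

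What remains is narrower. The Objective 4 text does not draw on the interviews or the repeated physician items. Absorption of the program into CSSS routine differs from continued links between organizations. Questions about timing asked only at month 40 depend on recall and are unlikely to recover links already lost. The stated limitation concerns length of observation, not the number of network-wide measurements.

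**Conclusion.** The point holds in a limited form. The dedicated network-wide measure for Objective 4 has one wave after the start, at project end, supplemented by one set of perceived-influence items per physician. That can support a conclusion about closer links and gives only weak support for long-lasting ones. The article does not say how the interviews or the repeated physician items would be used to judge duration.

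The consequence is for how far the Objective 4 conclusion can reach. No test, power figure or patient outcome is affected. The conclusion rests on the article's stated schedule and on the Additional files not being available. If the month-40 questionnaire asks when links began and whether they continue, the weakness is smaller, but a single retrospective wave would remain.

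**What to change.** Include the interorganizational collaboration items in the month-20 interview round and repeat the same items at month 40. The article says that the month-20 and month-40 collection tools will be constructed after the start-up data are analyzed, so there is room to do this. Ask informants in the same roles at both times, so that a change in answers does not merely reflect a change in who answers.

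State in the Objective 4 methods that durability will be judged from links or mechanisms present at both month 20 and month 40, supported by the physician items on specialized services at 12, 24 and 36 months. Presence at both times would show that a link or mechanism existed at two points 20 months apart; it would not prove that it was continuous in between.

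If this is not done, limit the Objective 4 conclusion to closer links at month 40 and leave long-lasting out of it.

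The cost is a few more items in an interview round already planned and a small extra burden on key informants in six CSSS. No new data collection wave is needed.
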